8.6 After inoculation

　　Video recording ends after 10 seconds of inoculation

　　FLACC scale evaluation by attendant

　　Collect adverse events, diseases, etc. up to 10 minutes after vaccination

8.7 At the time of cancellation

　At the time of discontinuation after use of TAK-01, the following evaluations and data collection will be conducted to the extent possible.

　 　FLACC scale evaluation by attendant

Imaging of immunization status and FLACC scale evaluation by FLACC scale evaluation committee members

Information gathering on adverse events, diseases, etc.

For research subjects not using TAK-01, reasons for discontinuation will be collected to the extent possible.

9. Criteria for discontinuation

If the principal investigator or research associate investigator (hereinafter referred to as "principal investigator, etc.") determines that it is impossible for the research subject to continue participation in the research for any of the following reasons, the research will be discontinued and the timing of the discontinuation or dropout, the reason for the discontinuation or dropout, and the progress, etc. will be noted on the CRF.

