6.3 Research Plan Treatment

　Cooling group: TAK-01 is cooled for at least 3 hours in a freezer (internal temperature: -16 to -20 degrees C), removed from the freezer, and allowed to permeate for 1 to 3 hours in ice water. The TAK-01 is then applied directly to the subject's vaccination site for 30-60 seconds, and inoculation is performed within 1 minute after the TAK-01 is removed.

　Uncooled group: TAK-01 is placed at room temperature (approximately 20 degrees Celsius) for at least 3 hours, and is applied directly to the subject's vaccination site for 30 to 60 seconds.

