6.5 Criteria for Discontinuation of Research Protocol Treatment

If you are unable to receive the vaccination after obtaining consent.

If the TAK-01 is not available to the research subject, or if the time to apply the TAK-01 is less than 30 seconds.

If the vaccination could not be administered within 1 minute after the TAK-01 was removed.

When it is difficult to observe as prescribed due to adverse events, etc.

When the principal investigator decides to discontinue the study

However, for study subjects using TAK-01, in addition to the 10-minute post-immunization observation, the FLACC scale evaluation will be performed immediately after immunization by an attendant and later by the FLACC scale evaluator after viewing the imaged video.

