14.1 Population to be analyzed

14.1.1 largest analysis set (full analysis set: FAS)

The population of study subjects enrolled in the study, for whom subcutaneous injections were administered, and for whom at least one efficacy endpoint was measured, will be the largest population for analysis (FAS).

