14.2 Target Number of Cases

　Target number of patients: 30 in the cooling group and 30 in the non-cooling group

Rationale: For the primary endpoint of FLACC, a two-sample t-test, assuming an effect size of 0.9, a risk rate of 5% (two-sided) and a power of 90% would require 27 cases in each group. Assuming a dropout rate of about 10% due to inadequate videotaping, etc., 30 cases were needed for each group.

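### No FLACC score is planned for a randomised, vaccinated child on whom the pack was not used, so the full analysis set excludes children by exposure after randomisation

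*Protocol*

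**What the plan says.** Allocation is made in REDCap after consent and eligibility (6.2.2, 8.3), and the assigned pack is used afterwards (8.4). Site staff know the allocation; children and attendants are meant not to (6.2.3).

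Section 6.5 lists the criteria for stopping protocol treatment. One is that the vaccination cannot be given. A separate one is "If the TAK-01 is not available to the research subject, or if the time to apply the TAK-01 is less than 30 seconds". The section then provides for the attendant's and the committee member's FLACC ratings after stopping, but only for children using TAK-01. Section 8.7 makes the same split: after pack use, both ratings and adverse events are collected where possible; without pack use, "For research subjects not using TAK-01, reasons for discontinuation will be collected to the extent possible". Section 9.2 only refers back to 8.7.

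The FAS (14.1.1) takes enrolled children who received the injection and "for whom at least one efficacy endpoint was measured". It does not mention pack use.

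**The concern.** A missing pack and a missed vaccination are separate criteria in 6.5, so a child can be randomised, not have the pack applied, and still be injected. The child then has a pain response that could be scored, but the plan does not ask for it. The collection rule, rather than the FAS definition, thus turns the FAS into a set of children who were exposed to the pack.

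An analysis set that depends on what happened after randomisation loses the protection of randomisation if the excluded children differ in outcome and the losses differ between arms. Both are possible here. The rationale for the exclusion criteria (5.2) expects a violently crying child to reject the pack, and crying is itself a FLACC component. Only crying that began before consent is screened out. One arm receives a cold pack and the other a pack at room temperature, so rejection need not be equally common. The statistical analysis plan cannot repair the gap, because it cannot recover scores that were never taken.

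**Working it through.** **1. The plan's own figure.** Section 14.2 specifies "a two-sample t-test, assuming an effect size of 0.9", with "a risk rate of 5% (two-sided) and a power of 90% would require 27 cases in each group". Using the noncentral t distribution, n = 26.94, so 27 per group, with power 0.9006. Allowing for 10% dropout, 27 / (1 − 0.10) = 30. The stated size reproduces, and scoring every vaccinated child would not change it.

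**2. The rules side by side.**

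| Randomised child | FLACC planned? | In the FAS? |
|---|---|---|
| Pack used as planned, vaccinated | Both ratings | Yes |
| Pack used for under 30 s, or injection late | Both ratings (6.5, 8.7) | Yes, once scored |
| Pack not used, vaccinated | Reason only (8.7) | No, as no endpoint is measured |
| Not vaccinated | Not relevant | No, by definition |

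Only the third row is at issue. The adverse-event endpoint is not affected in the same way, because 14.1.3 defines safety on children treated with the pack.

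**3. Power.** With 30 controls and an effect of 0.9 SD, power is 0.929 with none lost from the cooled arm, 0.925 with 1 lost and 0.915 with 3 lost. Power is not the problem.

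**4. Bias.** Suppose k of 30 children are lost from one arm and would have scored d SD above the rest of that arm. The full-arm mean is the mean of the rest plus (k/30) × d, so the analysed mean is too low by (k/30) × d. With losses in both arms, the net bias in favour of cooling is (k_cooled × d_cooled − k_control × d_control) / 30. It vanishes if d = 0 in both arms or if the losses balance.

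The documents give neither k nor d. The table assumes losses in the cooled arm only. The case k = 3 uses up that arm's whole dropout allowance (10% of 30). The last column is the two-sided rejection rate at nominal 5% when there is no true effect. It comes from a noncentral t with λ = b / √(1/30 + 1/(30 − k)) and 58 − k degrees of freedom, where b is the bias and the SD is taken as unchanged.

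| k | d (SD) | Bias b (SD) | b / 0.9 | Rejection rate |
|---|---|---|---|---|
| 1 | 0.5 | 0.017 | 1.9% | 0.0505 |
| 1 | 1.0 | 0.033 | 3.7% | 0.0518 |
| 1 | 1.5 | 0.050 | 5.6% | 0.0541 |
| 3 | 0.5 | 0.050 | 5.6% | 0.0539 |
| 3 | 1.0 | 0.100 | 11.1% | 0.0659 |
| 3 | 1.5 | 0.150 | 16.7% | 0.0861 |

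For the last row, λ = 0.15 / √(1/30 + 1/27) = 0.15 / 0.265 = 0.57.

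**The case against.** The strongest reply is that the documents do not show the loss to be differential or informative. Much of that stands.

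- **Pack readiness.** A reader might infer that the cooled arm loses more children because its pack is harder to have ready: "TAK-01 is cooled for at least 3 hours in a freezer" and then 1 to 3 hours in ice water, against at least 3 hours at room temperature in the control arm. The protocol nowhere says that readiness causes non-use or that non-use differs by arm. Freezer time has no upper limit, so packs can be kept in stock, and pack management is left to a separate procedure (6.6). A logistic failure also gives no reason to expect higher pain scores, and with d = 0 the bias is zero.
- **Rejection by the child.** This is the only failure to apply the pack that the protocol explains. It could be related to pain scores, but a pack is pressed on the arm in both groups, so rejection can occur in both. Children already crying violently are excluded.
- **Scoring is not forbidden.** Video starts before pack use (8.4), 8.6 lists the attendant's rating without conditions, and a non-user who happened to be scored would be in the FAS. The accurate statement is that no FLACC is planned for these children.
- **Size.** Larger losses, such as 5 of 30 in one arm (17%), go beyond the plan's own allowance: "Assuming a dropout rate of about 10% due to inadequate videotaping, etc., 30 cases were needed for each group". They should not be used to size the problem.
- **Exploratory aim.** The objective is exploratory, but 14.4 treats the effect as confirmed on one two-sided 5% test, so the analysis set still matters.

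These points limit the cause and the size. They do not remove the collection rule or its effect on the FAS.

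**Conclusion.** The point holds as a gap in planned outcome collection. Sections 6.5 and 8.7, read with 14.1.1, remove randomised and vaccinated children from both FLACC endpoints because the pack was not used.

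The resulting bias is conditional. It needs non-use to be related to distress or pain response, and to differ between a cold and a room-temperature pack. The documents establish neither. If non-use is unrelated to pain response, the bias is about zero. Under the assumptions above (1 to 3 of 30 lost from the cooled arm only, 0.5 to 1.5 SD above the rest) it is about 0.02 to 0.15 SD in favour of cooling, or 2% to 17% of the planned effect, and the true type I error is 0.05 to 0.09. The documents do not support a claim that pack preparation causes unequal loss between the arms. The sample size of 30 per group is unaffected.

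**What to change.** In 6.5 and 8.7, plan the video and both FLACC ratings for every randomised child who is vaccinated and whose consent is not withdrawn, whether or not TAK-01 was used. State in 14.1.1 that these children stay in the FAS in their allocated arm. Report the number of non-users and the reasons by arm.

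The cost is a wording change. Recording already starts before pack use and the attendant already scores, so no visit or equipment is added. There are two small downsides. First, the contrast is slightly diluted: if 3 of 30 cooled children get no cooling, an effect of 0.9 SD becomes 0.9 × (1 − 3/30) = 0.81 SD, and with 1 of 30 it becomes 0.87 SD. This is a shift towards no difference, and the per protocol set (14.1.2) remains as a complement. Second, raters can see that no pack was applied to these few children, so the blinding device is absent for them; the report by arm shows how many are concerned.

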9.1 Criteria for Discontinuation of Study Subjects

(1) If the substitute consents to withdraw his/her consent to participate in the clinical research after the commencement of the clinical research

(2) If the research subject is found not to meet the eligibility criteria

(3) If the Principal Investigator, etc. determines that the research subject is unable to comply with the research protocol

(4) Other cases in which the principal investigator determines that the research should be discontinued.

9.2 Post-Cancellation Measures

　At the time of discontinuation, the items listed in 8.7 should be evaluated whenever possible.

10. Handling of Adverse Events, Diseases, etc.

Adverse events and diseases are defined as follows

10.1 Definition of adverse events

All unfavorable events or unintended illnesses or signs of illness (including abnormal laboratory values) that occur in research subjects using TAK-01. This refers to all unfavorable events or unintended illnesses or signs of illness (including abnormalities in clinical laboratory values) that occur in research subjects using TAK-01, regardless of whether they are causally related to this study.

10.2 Serious adverse events

An adverse event is defined as a serious adverse event if any of the following apply

(1) Deadly

(2) May lead to death

(3) Those requiring hospitalization or an extended period of hospitalization for treatment

(4) Obstacles

(5) Threat of failure

(6) Other serious cases according to (1) through (5)

(7) Congenital diseases or anomalies in subsequent generations

10.2.1 Reporting procedures for serious adverse events

(1) If a serious adverse event occurs, the investigator at the site of the study should report the cause and effect of the event to the investigator. Regardless of whether or not there is a relationship, report the occurrence to the principal investigator at the site when you become aware of it.

(2) The principal investigator shall report the occurrence of a serious adverse event to the administrator of the institution using the "Uniform Form 9" and then to the principal investigator as soon as he/she becomes aware of the occurrence of the event.

(3) The Principal Investigator will report the obtained "Uniform Form 9" to the Director of the Principal Investigator's site and then to the Certified Clinical Research Review Board ("CRB"), and provide the information to other principal investigators.

The "Uniform Form 9", which is defined as the reporting form for serious adverse events, shall be used for the reporting of serious adverse events for diseases, etc. as defined in 10.3. This is a reporting form for the occurrence of an event that meets (1) to (7) of 10.2, although it is a reporting form for the occurrence of an event that meets (1) to (7) of 10.2. This is to be used in lieu of the Report Form. The "Uniform Form 9" is used in lieu of the Reporting Form. The report should be supplemented by using the appropriate sections of the standardized form "Form for Detailed Description" for the basis for the determination.

10.3 Definition of Disease, etc.

The period from the use of TAK-01 until the end of observation, including any illness, disability, death, or infection suspected to have resulted from the conduct of this study, as well as any abnormal laboratory values or symptoms. The details of the procedures for reporting the occurrence of illness, etc., as stipulated in the Clinical Research Act, are described in the "Procedures for handling the occurrence of illness, etc.

11. Handling of defects

11.1Definition of defects

This term refers to any problems with the quality, safety, or performance of the TAK-01, such as breakage or malfunction, regardless of whether the problem is caused by the design, delivery, storage, or use of the TAK-01.

If a problem occurs, the research physician must report it to the principal investigator as soon as he or she becomes aware of the problem.

The investigator will report the results to the principal investigator using the "Uniform Form 9. The principal investigator reports to the principal investigator using the "Uniform Form 9.

Failures that should originally be described in the "Uniform Form 9" are only those cases where it is judged that the failure of a medical device used in clinical research may cause disease, etc. However, the "Uniform Form 9" should also be substituted for failures in cases where it is not judged that there is a risk of causing disease, etc.

In addition, any defects that are determined to have the potential to cause health hazards shall be reported in accordance with the "Procedures for handling cases of illness, etc.".

12. initiation, suspension, discontinuation and termination of clinical research

12.1 Initiation of Clinical Research

In conducting this study, the investigator shall prepare an implementation plan (Form 1), attach the necessary documents, and obtain the opinion of the CRB described in said implementation plan. The investigator shall submit said implementation plan to the Minister of Health, Labour and Welfare by registering it in the Japan Registry of Clinical Trials ("jRCT"). The date when the information of the study is registered in jRCT and released to the public shall be the study start date. Consent of research subjects will not be obtained prior to the release of information.

　The principal investigator shall report to the CRB that he/she has submitted said implementation plan to the Minister of Health, Labour and Welfare, which has heard the opinion.

12.2 Criteria for Discontinuation or Suspension of an Entire Clinical Study

　The principal investigator will consider suspending or terminating the entire study if the clinical research meets the following criteria

　(1) In the event of unavoidable ethical or medical circumstances, such as the occurrence of an illness or other event for which a causal relationship to the conduct of this research cannot be denied and for which the risks associated with participation in this research are judged to outweigh the benefits to the research subjects.

　(2) When a serious nonconformity is found in the research protocol, etc.

　(3) If the significance of conducting this research is lost

12.3 Procedures for suspending an entire clinical study

12.3.1 Procedures for Suspension

When suspending the research, the principal investigator shall submit a change in the implementation plan (change in progress) to the CRB and the Minister of Health, Labour and Welfare without delay.

12.3.2 Procedures for reopening

The principal investigator will consider the necessity of revising the research protocol and various procedure manuals before resuming this study after interruption, and will obtain the CRB's opinion. If changes are necessary, they shall be made in accordance with "14. Changes in Research Protocol, Procedures, or Statistical Analysis Protocol, etc.". In addition, the changes in the implementation plan (changes in progress) shall be submitted to the CRB and the Minister of Health, Labour and Welfare without delay.

12.4 Procedures for discontinuation of the entire clinical research

12.4.1 Procedures for Discontinuation

　If the Principal Investigator discontinues this research, he/she shall notify the CRB of the discontinuation (Uniform Form 11) and submit a Notification of Discontinuation of Specified Clinical Research (Ordinance Form 4) to the Minister of Health, Labour and Welfare within 10 days of the date of discontinuation.

The principal investigator shall submit notifications of changes in the implementation plan, disease reports, periodic reports, etc., from the discontinuation of this research until the completion of observation, etc., of all research subjects and the termination of this research.

The Principal Investigator will terminate the study in accordance with "11.5 Termination of Clinical Research" within one year from the later date of either discontinuation of the study or completion of observation of all study subjects.

12.5 Termination of Clinical Research

　The principal investigator will prepare a primary endpoint report within one year after the end of the collection period for the primary endpoints and a summary report and summary report within one year after the end of the collection period for all endpoints.

When the Principal Investigator has prepared a summary of the primary endpoint report or summary report and summary report, he/she shall promptly submit it to the administrator of the implementing medical institution.

13. Clinical Research Period

April 1, 2021 - September 30, 2022

Enrollment period: after publication of jRCT - March 2022

Observation period: from obtaining consent to 10 minutes after vaccination is administered

14. Analysis targets and statistical analysis methods

14.1 Population to be analyzed

14.1.1 largest analysis set (full analysis set: FAS)

The population of study subjects enrolled in the study, for whom subcutaneous injections were administered, and for whom at least one efficacy endpoint was measured, will be the largest population for analysis (FAS).

14.1.2 Subject population conforming to the research protocol (per protocol set: PPS)

The population of patients included in the FAS who are free of material research protocol violations will be defined as the population of subjects (PPS) who conform to the research protocol. Significant study protocol violations will be defined by the principal investigator and the statistical analyst by database fixation after completion of the study.

14.1.3 Population for Safety Analysis

All cases enrolled in the study and treated with TAK-01 will be included in the analysis.

14.2 Target Number of Cases

　Target number of patients: 30 in the cooling group and 30 in the non-cooling group

Rationale: For the primary endpoint of FLACC, a two-sample t-test, assuming an effect size of 0.9, a risk rate of 5% (two-sided) and a power of 90% would require 27 cases in each group. Assuming a dropout rate of about 10% due to inadequate videotaping, etc., 30 cases were needed for each group.

14.3 Data Handling

14.3.1 Data Handling

Abnormal data, including outliers, will be examined before statistical analysis is conducted. In the event that a case deviating from the research protocol is found, the impact of the deviation on the efficacy evaluation of the case will be examined by the principal investigator and the statistical analysis supervisor before the database is fixed after the completion of the study, and the handling of each case will be determined individually.

14.3.2 Handling of Data on Discontinued Research Cases

Data collected up to the time of discontinuation of the study will be used as research data. However, if the consent for the use of the data is withdrawn from the surrogate consentor, the data will not be used.

14.4 Statistical Analysis Items and Analysis Plan

To confirm the effect of pain relief by cooling the subcutaneous injection inoculation site in young children, the FLACC score after subcutaneous injection will be compared with the non-cooling device group as an index. When the null hypothesis (the number of FLACC points at the time of subcutaneous injection after cooling by the cooling device = the number of FLACC points at the time of subcutaneous injection without cooling) is rejected at a significance level of 5% on both sides, it is judged that the effect of cooling the subcutaneous injection site with the cooling device on pain relief is confirmed.

Details of analyses not described in this protocol will be described in the "Statistical Analysis Plan" prepared by the person responsible for statistical analysis.

　14.4.1 Aggregation of Patient Background Information

Summary statistics (number of cases, mean, standard deviation, minimum, median and maximum) for quantitative variables and number of cases/percentage (%) for qualitative variables are obtained for demographic and other baseline characteristics for each group.

　14.4.2 Efficacy Analysis

Primary Endpoint

The FLACC scores after subcutaneous injection by a third party will be compared between groups by means of an unpaired t-test. For each group, summary statistics of FLACC scores (number of cases, mean, standard deviation, minimum, median and maximum) and 95% confidence intervals of the difference in means will be calculated.

secondary endpoint

The FLACC scores after subcutaneous injection of the attendant will be analyzed in the same manner as the primary endpoint.

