6.1.1 Types and Methods of Clinical Research

Multicenter, single-blind, blind assessment, randomized (allocation factor: institution), two-parallel group comparison

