6.1.2 Explanation of the relevance of the study design

　　The study was multicenter and single-blind because the technique of pressing TAK-01 to the injection site makes it difficult to blind the investigators.

　Although applying a cooling pack to the vaccination site is not a standard treatment, the comparison was made between the cooling group and the non-cooling group, rather than between the TAK-01 use group and the non-use group, in order to blind the attendants and the FLACC scale evaluation committee members who were to conduct the FLACC scale evaluation.

　Although it is possible that the 　study subjects themselves could be blinded, the age range was limited to 3-6 years to reduce the risk of such a split, and a blind assessment method by the FLACC scale assessors was used for the primary assessment.

　Because the immunization procedure is also considered a pain factor, the facility was used as an allocation factor to divide the patients into two groups within the facility: a cooling group and a noncooling group.

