6.2.2 Method of Randomization

　After consent is obtained, the investigators at the implementing institution will randomly assign the facility as the allocation factor using the REDCap system.

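### Children are allocated within institution because institution bears on pain, but the primary t-test leaves institution out and so overstates the standard error

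*Protocol*

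**What the plan says.** Section 6.1.1 describes the trial as "randomized (allocation factor: institution), two-parallel group comparison". Section 6.1.2 gives the reason, "Because the immunization procedure is also considered a pain factor", and the consequence: "the facility was used as an allocation factor to divide the patients into two groups within the facility". Section 6.2.2 repeats that the investigators "will randomly assign the facility as the allocation factor using the REDCap system". It does not say whether blocks, minimization or another method secures the balance.

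Section 14.4.2 fixes the primary analysis: "The FLACC scores after subcutaneous injection by a third party will be compared between groups by means of an unpaired t-test". Summary statistics are given by group, and "95% confidence intervals of the difference in means will be calculated". No institution term appears in the test or the interval, and the attendant's FLACC score is to be analysed in the same way. Section 14.2 sizes the trial for a two-sample t-test, and section 14.4 sets a two-sided 5% decision rule.

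Section 14.4 leaves to the SAP only the details of analyses that the protocol does not describe. The primary test is described, so it is fixed here.

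**The concern.** The protocol treats the facility as relevant to the outcome, balances on it, and then analyses the data as if it had not. When arms are balanced within site, a site with generally higher FLACC scores contributes equally to both arms, and its effect cancels from the difference in means. The pooled standard deviation in an unpaired t-test still contains the spread between sites. The test therefore judges the difference against more noise than the design leaves in it.

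Three things follow if sites differ as section 6.1.2 supposes. The reported 95% interval is wider than the design justifies. The true type I error is below the declared 5%. Power is given away in a trial of only 60 children. The objective is exploratory, so the precision of the estimate matters as much as the test.

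**Working it through.** **The plan's own figure.** Section 14.2 assumes an effect size of 0.9, two-sided 5%, 90% power and about 10% dropout. With n per arm, the noncentrality is 0.9 × √(n/2). At n = 27 it is 0.9 × √13.5 = 3.31, and the exact power with 52 degrees of freedom is 90.06%. At n = 26 the power is 88.9%. So 27 per arm is right, and 27/0.9 = 30 per arm. The sample size reproduces.

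**Inputs not in the protocol text.** These are the share ρ of FLACC variance due to institution, the number of sites and their sizes. Assumed: ρ from 0 to 0.30; 2, 3 or 5 sites of near-equal size; arms balanced within site; 27 evaluable children per arm; total SD of 1 before the treatment effect.

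**Closed form.**
- SE that the t-test reports: about √(2/27) = 0.272.
- True SE under within-site balance: √(2(1 − ρ)/27), which is 0.258, 0.243 and 0.228 at ρ = 0.10, 0.20 and 0.30.
- Ratio: 1/√(1 − ρ) = 1.05, 1.12 and 1.20.
- Approximate true type I error: 2Φ(−1.96/√(1 − ρ)) = 2Φ(−2.07), 2Φ(−2.19) and 2Φ(−2.34), or 3.9%, 2.8% and 1.9%.

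**Simulation with the site share held at exactly ρ** (3 sites, 40,000 runs per cell; each pair is t-test / model with institution):

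| ρ | Type I error | Power at 0.9 SD | Power at 0.6 SD | Mean reported SE |
| --- | --- | --- | --- | --- |
| 0 | 4.9% / 4.9% | 90.2% / 90.1% | 57.8% / 57.8% | 0.271 / 0.271 |
| 0.05 | 4.4% / 5.1% | 90.6% / 91.4% | 58.2% / 60.4% | 0.271 / 0.264 |
| 0.10 | 3.9% / 5.0% | 91.1% / 92.7% | 58.5% / 62.7% | 0.272 / 0.257 |
| 0.20 | 2.8% / 5.0% | 92.1% / 95.1% | 59.1% / 68.2% | 0.272 / 0.242 |
| 0.30 | 2.0% / 5.1% | 93.6% / 97.3% | 58.8% / 73.3% | 0.273 / 0.227 |

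Two or five sites give nearly the same figures.

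**Simulation with site effects drawn at random in each run** (3 equal sites, 27 per arm). The realised share varies between runs. With K sites, the realised between-site variance averages (K − 1)/K of its nominal value, which is two thirds for K = 3, so the effect is milder. At nominal ρ = 0.10, 0.20 and 0.30:
- Type I error of the t-test: 4.2%, 3.7% and 3.0%.
- 95% CI half-width: 0.535, 0.526 and 0.515 SD unadjusted, against 0.517, 0.487 and 0.456 SD adjusted, which is about 3%, 7% and 11% narrower.
- Power at 0.6 SD: 59% to 62%, 62% to 68%, and 64% to 74%.
- Power at 0.9 SD: 92%, 93% and 95% unadjusted, against 93%, 95% and 97.5% adjusted.

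Five sites of 10 children give type I errors of 3.9%, 3.1% and 2.7%. At a 5% share with three sites, the gain in power at 0.6 SD is about 1 point.

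**The case against.** The strongest reply is that the harm is conditional and mild. The standard error is too large only if institution explains a real share of FLACC variance and the allocation does balance arms within site. The protocol gives no size for the first and no method for the second. Sites may also be unequal. With three sites of 42, 6 and 6 children and random site effects, the t-test's type I error is 4.7%, 4.2% and 3.8% at shares of 10%, 20% and 30%, and adjustment narrows the interval by only about 2%, 4% and 7%.

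The error is also in the safe direction. It does not inflate false positives or bias the estimate, and a positive result would stand. The 0.6 SD effect is not the protocol's. At the planned 0.9 SD, power is at least 90% with either analysis, and the test agrees with the sample-size calculation. Balancing by site also protects against chance imbalance whatever the analysis, so it is not wasted.

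All of this limits the size, and it stands to that extent. It does not remove the mismatch. Section 6.1.2 itself asserts that the procedure affects pain and that the groups are formed within facility. Section 14.2 gives no source for an effect as large as 0.9 SD, so performance at smaller effects is relevant. At ρ = 0 the adjusted model loses nothing visible, so uncertainty about ρ is no reason to prefer the t-test. Leaving the matter to the SAP does not answer it either, because an institution term there would change a primary analysis that the protocol has already stated.

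**Conclusion.** The concern holds. The primary and attendant FLACC analyses omit the factor on which children are allocated. On the protocol's own premise, the standard error and confidence interval are then too large and the test is conservative. Across assumed institution shares of 10% to 30%, the true type I error is about 4% down to 2–3%, depending on how site effects are modelled. The power given up is about 1 to 4 points at 0.9 SD and roughly 2 to 15 points at 0.6 SD. These figures rest on near-equal sites and on arms balanced within site. At a share of 5% or with one dominant site the effect is small.

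The mismatch and its direction are certain on that premise; its size is not. This is a loss of efficiency that should be corrected. It does not threaten validity, and the sample size need not change.

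**What to change.** In section 14.4.2, replace the unpaired t-test by a linear model for the FLACC score with treatment and institution as fixed effects. Report the adjusted mean difference with its 95% confidence interval and p-value, for both the evaluator's and the attendant's score. Fix a rule for pooling very small institutions before unblinding. Keep the unpaired t-test as a supportive analysis.

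The cost is a sentence or two in section 14.4.2 and the matching text in the SAP. No further children or data are needed. The model uses one degree of freedom for each institution beyond the first, which is negligible with few sites and 54 to 60 children.
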